#### Sample size calculation

A priori calculation of the sample size to test the IG’s superiority to the CG in primary outcomes (comparison of adjusted mean values in two groups) was performed with the software *“Power and Precision*”. We used an effect size of 0.30, power of 0.80 and a Bonferroni adjustment (5% / 2 = 2.5%) due to the multiple testing of two primary outcomes. The design effect due to clustering of the practices [30] is DE = 1 + 0.01 × (10–1) = 1.09 with an assumed intra-cluster correlation of 0.01 [31] and a number of cases per cluster of *N* = 10. With a 2:1 distribution in the IG and CG, a sample size of *N* = 320 (IG) and *N* = 160 (CG) without design effect and *N* = 349 (IG) and *N* = 175 (CG) with design effect was calculated. Due to an expected dropout of approximately 35% a sample size of *N* = 537 (IG) and *N* = 270 (CG) is necessary. However, health economics evaluation including a budget impact analysis requires a relatively large variance of cost values (150% standard deviation). Based on a power of 0.80, an alpha level of 5% and an effect size of 30%, the number of cases is *N* = 590 (IG) and *N* = 295 (CG) without design effect and *N* = 643 (IG) and *N* = 322 (CG) with design effect. Given the assumed dropout of approximately 35%, this results in the desired recruitment target of *N* = 1.000 (IG) and *N* = 500 (CG).

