### Data management

A seven-digit patient research ID (three-digit number for the practice, two-digit number for the attended physician and a consecutive two-digit number per patient attending the physician) is allocated to each participating patient. A database with these research IDs and the associated names and contact details of the patients (participation list) is created. Due to the research IDs the questionnaires of the three measurement points can be matched. Further, the research IDs of the questionnaires are definite relatable to the log-in names of the portal (user data) and the research IDs used for the routine data of the health insurance. The analysing institutions keep a record about the return of the patient questionnaire in an Excel-Sheet. The ID of returning questionnaires will be reconciled with the ID of cases in the SPSS data files.

Codebooks will be prepared for the questionnaires. Scanning is used for the data entry of the patient questionnaires. The team member entering the data can immediately correct data which was incorrectly inserted by the computer system. The data of 10% randomly selected questionnaires will be double-checked. If more than 5 ‰ of the data entries are incorrect, all data will be entered twice. The patient questionnaires will be checked for plausibility of age and gender. The checks include that the gender is reported identically across all three measurement points and that there is only 1 year of difference between the measurement points t0 and t2. For all items there will be a range check of data values. As the physician questionnaires are completed primarily online, there will be no double entry of data but there will be plausibility checks comparable to the patient questionnaires.

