### Statistical methods

#### Analysis of patients‘questionnaire data

Based on the analysis of the missing outcome data, simple or multiple imputation may be considered. Dropout analysis will be performed using Chi-Squared tests for nominal variables, Mann–Whitney U tests for ordinal variables and t-tests for interval variables. The significance level is set at *p* = 0.05. Special attention is paid to the hierarchical data structure of the questionnaire data. Due to the cluster randomisation, patients’ responses cannot be presumed as independent, as the patients are nested within practices. Because of this, separate two-level (patient – practice) multilevel linear models for both measurement points (t1 and t2) will be calculated. Treatment allocation (IG vs. CG) will be used as predictor variable in the multilevel linear models. The fit of the multilevel linear models are tested using amongst others the Akaike’s information criterion and Schwarz’s Bayesian criterion. Despite the randomisation a propensity score adjustment is considered in case of a potential imbalanced allocation [32]. Intraclass correlations are calculated to assess the cluster (practice) dependency of the responses.

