#### Analysis of physicians‘questionnaire data

The data analysis is primarily exploratory. The primary outcomes will be analysed using inferential statistics methods. IG and CG will be compared across the three measurement points. Statistically adjusted comparisons of means between IG and CG as well as across the three measurement points (using propensity scores) will be conducted. The characteristics of the practices and the user data of the online platform will be used as control variables. Before the calculations, the missing data processes, singular missing data and the drop-out of patients will be analysed. Recommendations regarding the handling of missing data in order to correct information biases will be considered [33]. If data is missing completely at random or missing at random, missing data will be imputed using the expectations-maximation algorithm. Moreover, there will be sensitivity analyses to assess the influence of missing data processes.

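### Filling missing physician scores once by EM and then testing them gives standard errors that are too small, or a diluted group effect, when whole scores are missing

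*Protocol article*

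**What the plan says.** Under the analysis of the physicians' questionnaire data, the article makes a firm commitment: "If data is missing completely at random or missing at random, missing data will be imputed using the expectations-maximation algorithm". The same paragraph announces an analysis of the missing-data processes, of single missing values and of drop-out. It says that published recommendations on missing data will be considered, and it adds: "Moreover, there will be sensitivity analyses to assess the influence of missing data processes". It names no multiple imputation, added residual noise, bootstrap or other variance correction for these data.

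On the status of the analysis it says first "The data analysis is primarily exploratory" and then "The primary outcomes will be analysed using inferential statistics methods". Table 2 lists physician-rated communication among the primary outcomes, measured at t0, t1 and t2. The primary hypothesis in the Methods also covers ratings by general practitioners. These scores will therefore be compared between groups with significance tests.

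**The concern.** EM imputation, as normally understood, replaces each gap with the value predicted from the fitted model. A later comparison of adjusted means cannot tell these predictions from observations. It counts physicians who supplied no score as full cases and sees no residual scatter in their values.

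Two outcomes are possible, depending on an imputation model that the article does not describe. If group is a predictor, the estimate is sound but its standard error is too small, so tests reject too often. If group is left out, physicians with missing scores in both arms receive predictions from one common line, and the difference between arms shrinks. The two are alternatives and do not occur together. Each arises even when data are missing completely at random, the most favourable case under the article's own rule.

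At stake are the tests and intervals for physician-rated communication.

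**Working it through.** **Inputs**
- 150 general practitioners, with practices allocated 2:1 (Participants and recruitment). This gives 100 vs 50 physicians if they split as the practices do, which is an assumption.
- Effect of 0.30 standard deviations: the planning effect in the Sample size calculation, borrowed here for physicians.
- Physician missing rate m: not given. Assumed 5%, 10%, 20% and 35%.
- Correlation of t0 and t1 scores: not given. Assumed 0.5, with 0.3 to 0.7 as the range.

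**Where the 35% comes from.** The only dropout figure stands in the Sample size calculation ("Due to an expected dropout of approximately 35" per cent). That calculation reproduces as one for patients: 320 × 1.09 = 348.8 and 160 × 1.09 = 174.4, stated as 349 and 175; then 349 / 0.65 = 536.9 and 175 / 0.65 = 269.2, stated as 537 and 270. The 35% is therefore a patient rate, and for physicians it is only an upper scenario.

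**Group in the EM model.** Imputed values lie exactly on the fitted line, so they add no residual scatter but do add to the case count.
- The residual variance is estimated at about (1 − m) times its true value.
- The test divides by n cases where only n(1 − m) were observed.
- The reported variance is therefore about (1 − m)² times the true variance, and the reported standard error about (1 − m) times the true one.
- Type I error at nominal 5% is about 2 × [1 − Φ(1.96 × (1 − m))].

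**Group not in the EM model.** A share m of each arm carries no group difference, so the expected estimate is about 0.30 × (1 − m).

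**Simulation.** 100 vs 50 physicians, t0 complete, t1 missing completely at random, analysis of covariance on t0, 4,000 runs per setting. The 10%, 20% and 35% rows cover correlations 0.3 to 0.7; the 5% row is for correlation 0.5 only.

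| Missing | Type I error, group in model: formula | Simulated | Effect of 0.30, group not in model: formula | Simulated |
|---|---|---|---|---|
| 5% | 6.3% | about 6% | 0.285 | about 0.29 |
| 10% | 7.8% | 7.3–8.8% | 0.270 | 0.27 |
| 20% | 11.7% | 11.7–12.7% | 0.240 | 0.24 |
| 35% | 20.3% | 20.3–22.0% | 0.195 | 0.19 |

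At 35% missing and correlation 0.5, with group in the model, the reported standard error averages 0.121 against a true 0.189: 1 − 0.121/0.189 = 36% too small. Analysing the observed cases alone kept the type I error between 4.6% and 5.7% in the 10% to 35% settings. EM without group kept it between 4.7% and 5.6%, so in that version the harm is dilution only.

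**Isolated missing items.** For a nine-item scale (inter-item correlation 0.5 assumed, group in the EM model, 2,000 runs), rejection under no effect was 4.6%, 6.0% and 5.4% with 5%, 10% and 20% of items missing. That is close to the nominal 5%.

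**The alternative.** Multiple imputation with group and t0 score (20 imputations, Rubin's rules, 10,000 runs, 35% missing, correlation 0.5) gave a reported standard error of 0.190 against a true 0.190. Type I error was 4.9%, and the estimate was 0.301 for a true 0.30.

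**Limits.** The simulations ignore clustering of physicians within practices, use one follow-up time, and do not model the planned propensity adjustment.

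**The case against.** The strongest reply is that the article does not say that EM will fill absent questionnaires. It mentions single missing values as well as drop-out, the instruments are multi-item scales, and item-level EM does little harm. This stands in part. The inflation applies only to whole missing scores. But the commitment covers missing data without limit, in a paragraph that also names drop-out, so whole scores fall within it as written.

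Second, the article never calls the imputation single. That is an inference. It is the natural one, since EM is the only method named for physicians and no variance step follows.

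Third, the analysis is called primarily exploratory, published recommendations are to be considered and sensitivity analyses are planned. This lowers the severity. It does not repair the main result: the sensitivity analyses address the influence of the missing-data processes, whereas the standard error here is wrong even when that process is harmless.

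A reader might go further in three ways, none of which the document supports:
- *That the false-positive rate is about 20%.* This applies a patient dropout rate to physicians, who are surveyed mainly online and paid at the end of the survey period. Their loss may be much smaller.
- *That the patient analysis has the same fault.* There the article says only "Based on the analysis of the missing outcome data, simple or multiple imputation may be considered". No method is fixed and multiple imputation is expressly allowed. The final choice may properly be left to an analysis plan.
- *That the rule fails because missingness at random cannot be verified from the data.* This is true of the assumption, but the mixed model and multiple imputation rest on it too, so it does not favour them over EM.

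**Conclusion.** The point holds, within limits. The article fixes a method for missing physician data that, read as one filled-in value per gap, gives wrong tests or diluted estimates for whole missing scores on outcomes listed as primary. The type I error is modest at low missing rates (about 6% at 5% missing) and serious only if physician loss is substantial (12–13% at 20% missing). The 20–22% at 35% is an upper scenario and not a forecast. If group is left out of the EM model, the type I error is kept but the effect shrinks by about the missing share.

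These sizes rest on assumed missing rates, a 100:50 split, t0–t1 correlations of 0.3 to 0.7 and data missing completely at random. The direction of the error does not depend on the exact rate. Severity is limited: the physician analysis is primarily exploratory, the trial was sized on patients, and the patient comparison is not shown to be affected. The change is still worth making, because the physician tests bear on the primary hypothesis and the remedy is cheap.

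**What to change.** In the section on the physicians' questionnaire data, replace EM imputation of missing scale scores with one of the following, named in advance as the main analysis:
- a likelihood-based mixed model on all observed t0, t1 and t2 scores, with no filling-in; or
- multiple imputation with group, t0 score and practice in the imputation model, combined by Rubin's rules.

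EM may stay for isolated missing items within a scale that is otherwise completed; say so explicitly. Keep the planned sensitivity analyses.

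The cost is a change of wording and some programming, with no new data. Reported intervals become wider: in the 35% scenario at correlation 0.5, the standard error goes from 0.121 to 0.190, a factor of 0.190/0.121 = 1.57. That width reflects the information actually collected.

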#### Analysis of the routine data

The health economic analysis will be conducted in two steps. First, the financial effect of the intervention from the health insurances’ perspective will be calculated using a Budget-Impact-analysis. This analysis considers the back-pain related in-and outpatient costs for the health care system and the costs related to days of sick leave, where available. In an initial sensitivity analysis the reported days of sick leave are assessed in an alternative way using the human capital method to prevent potential inconsistencies. Depending on the data security regulations (see data security manual), the results of the Budget-Impact-analysis will then be linked to the outcomes of informedness using an exploratory cost-effectiveness analysis. The aim is to assess two cost-effectiveness ratios: additional costs per unit of ‘patients’ self-reported knowledge’ and additional costs per unit of ‘patients’ perceived informedness’. For the cost-effectiveness analysis confidence intervals will be calculated using the Fieller-theorem [34].

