## Methods

The GAP trial uses a prospective multi-centre, cluster-randomized parallel group design in order to evaluate whether the use of the GAP portal on back pain is superior to routine care. The GAP project consists of three phases. (1) Within the pilot phase, the portal will be tested for usability by physicians and patients and adapted according to the pilot findings (Additional file 1: Development and piloting of the GAP portal). (2) The main trial (second phase) evaluates the effects on pre-defined outcomes in general practitioners and patients with back pain (Table 1). (3) Within the third phase, the potential benefit of web-based information for health problems other than back pain will be analysed (Additional file 2: Expanding of the GAP portal).

**Table 1 Tab1:** PICO question of the GAP trial

Research Question	What are the effects of using the back pain internet portal compared to standard care in patients with back pain?
Population	150 general practitioners and 1500 back pain patients in Northern Bavaria
Intervention	Using the portal during (physician) and after (patient) the consultation.
Comparison	Routine consultation (no use of the portal)
Outcomes	1. Physicians‘and patients’ informedness 2. Physician-patient-communication 3. Patients‘health literacy and self-efficacy expectation 4. Days of sick leave 5. Back pain related health costs

*Hypothesis on primary outcomes:* (1) After the consultation, the informedness and the quality of the physician-patient communication are rated significantly higher by general practitioners and patients who use the portal (intervention group, IG) than by those who do not (control group, CG, consultation as usual).

*Hypotheses on secondary outcomes:* (2) 3 weeks after the consultation, the patients’ informedness, health literacy and self-efficacy are significantly higher among those who use the portal than among those who do not. (3) 3 months after consultation, the number of days of sick leave as well as the utilization of health system resources is significantly lower among patients who use the portal than among those who do not.

*Design:* Prospective cluster RCT with pre-, post- and one follow-up-measurement and process evaluation.

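### Minor: if the portal works as hypothesised, the exploratory cost-effectiveness ratios will be negative, where neither the ratio nor its Fieller interval can be read as value for money

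*Protocol article*

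**What the plan says.** The protocol article, under Analysis of the routine data, sets out two economic steps. In the first, "the financial effect of the intervention from the health insurances’ perspective will be calculated using a Budget-Impact-analysis". In the second, subject to data security rules, those results are to be "linked to the outcomes of informedness using an exploratory cost-effectiveness analysis". The output of this second step is named: "The aim is to assess two cost-effectiveness ratios: additional costs per unit of" self-reported knowledge, and likewise per unit of perceived informedness. The interval method is also named: "For the cost-effectiveness analysis confidence intervals will be calculated using the Fieller-theorem". The section mentions no cost-effectiveness plane, net benefit, value per unit of informedness, or rule for a negative ratio.

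The hypotheses under Methods give the expected direction of both components. For the effect, "the informedness and the quality of the physician-patient communication are rated significantly higher by general practitioners and patients who use the portal" than by those who do not. For cost, at three months "the number of days of sick leave as well as the utilization of health system resources is significantly lower among patients who use the portal", compared with non-users. The Sample size calculation plans on 0.30 for the primary outcomes. For costs it assumes a standard deviation of 150% and "an effect size of 30%, the number of cases is" 590 and 295 before the design effect.

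**The concern.** Write dC for the cost difference and dE for the informedness difference, intervention minus control. The hypotheses put the trial at dC < 0 and dE > 0, so the ratio dC/dE is negative when the portal does what it is meant to do. Two difficulties follow.

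- **No ordering.** Saving 100 for a gain of 0.1 units gives -1000; saving 200 for a gain of 0.5 units, better on both counts, gives -400. Saving 100 for 0.5 units gives -200. Neither larger nor smaller is reliably better.
- **No sign.** Reversing both differences leaves the ratio and its Fieller set unchanged, so the summary alone does not show which of two opposite results was found.

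A separate difficulty arises if the portal has little effect on informedness: the Fieller set then often has no finite limits. At stake is whether the step that links cost to informedness gives an insurer something usable.

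**Working it through.** **Inputs from the protocol.** Sample size calculation: cost SD 150% of the mean, 30% cost difference, 0.30 SD effect, 2:1 allocation, design effect 1.09, 643 and 322 patients with the design effect. Background: 1322 € per patient and year, 46% of it direct, so 1322 × 0.46 = 608 €.

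**Assumptions.** Mean cost 608 € (range to 1322 €; annual figures, for illustration only); the same 643/322 evaluable for informedness; effect in SD units; cost-effect correlation 0 (range -0.2 to 0.2).

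**1. The plan's own figures reproduce.** A two-sided 5% test with 80% power, difference 0.30, SD 1.5 and 2:1 allocation needs 590 and 295. Times 1.09 gives 643.1 and 321.6. Divided by 0.65 this is 990 and 496, against the rounded target of 1000 and 500.

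**2. Standard errors.**
- Effect: s = √(1.09 × (1/643 + 1/322)) = 0.0713 SD.
- Cost: 1.5 × 0.0713 = 0.107 of mean cost, or 65.0 € at 608 €.

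**3. How often the ratio is negative under the plan's alternatives.** dE/s = 0.30/0.0713 = 4.2, and dC/(1.5s) = -0.30/0.107 = -2.8. In 400,000 simulated trials with independent differences, the ratio was negative in 99.7%. With a true effect of 0.10 SD (assumed) and the same cost saving, it was negative in 91.8%.

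**4. Sign reversal.** The Fieller limits are the roots R of

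R²(dE² - z²vE) - 2R(dC·dE - z²cov) + (dC² - z²vC) = 0.

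Reversing both signs changes neither dE², dC² nor dC·dE, so with the same variances and covariance the roots are identical. With dC = ±182 € and dE = ±0.30:

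| Result | Ratio | 95% Fieller interval |
|---|---|---|
| Cheaper and better (-182, +0.30) | -608 | -1377 to -176 |
| Dearer and worse (+182, -0.30) | -608 | -1377 to -176 |
| Dearer and better (+182, +0.30) | +608 | 176 to 1377 |
| Cheaper and worse (-182, -0.30) | +608 | 176 to 1377 |

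For the first two rows, the pair is also identical at correlation -0.2 (-1260 to -192), at 0.2 (-1492 to -162), and at a mean cost of 1322 € (ratio -1322, interval -2994 to -382).

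**5. When the Fieller set is unbounded.** This happens when |dE/s| < 1.96.
- True effect 0.30 SD: about 1.2% of trials.
- True effect 0.10 SD (assumed): about 71%.
- No effect: 95%, which is 1 minus alpha by construction.

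**6. A summary that keeps the sign.** Incremental net benefit is λ·dE - dC, with variance λ²vE + vC at zero correlation. The λ values are assumptions, as the protocol gives none.

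| λ (€ per SD) | Cheaper and better | Dearer and worse |
|---|---|---|
| 0 | +182 (55 to 310) | -182 (-310 to -55) |
| 500 | +332 (187 to 478) | -332 (-478 to -187) |
| 1000 | +482 (293 to 672) | -482 (-672 to -293) |

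**The case against.** A reader might infer from the sign reversal that the trial cannot tell its hypothesised result from the opposite. The protocol does not support that. The budget impact analysis comes first and shows the direction of the cost difference. The multilevel models under Analysis of patients' questionnaire data show the direction of the informedness difference, and patient informedness is a primary outcome. The ratio cannot be computed without both. This stands, and it limits the point to the cost-effectiveness summary.

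A reader might also conclude that Fieller's method is the wrong tool. It is not: it is valid for a ratio, and an unbounded set correctly reports that the data do not exclude a zero denominator. At the planned effect this is rare. The 71% rests on an effect size that the protocol does not state.

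The analysis is also labelled exploratory, depends on data security rules, and is described in a condensed article; a plane or a dominance rule may stand in a fuller plan. That excuses missing detail. The ratios and their interval method, however, are stated choices, and they fit poorly with the stated hypotheses.

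Finally, one comparison of two arms leaves no set of options to rank by ratio. That is true, but the interval still has to be read: between -1377 and -176, neither end is the favourable one. Knowing the two signs identifies the quadrant but does not repair this.

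**Conclusion.** The point holds as a minor one, confined to the exploratory cost-effectiveness summary. Under the trial's own hypotheses the planned ratio is negative in about 99.7% of trials, where its size does not express value and where it and its interval coincide with those of the dearer-and-worse result. The coincidence is exact algebra and needs no assumption beyond equal variances and covariance. The 99.7% rests on the planning inputs, 643 and 322 evaluable patients for both measures, and independent cost and effect differences. The euro figures are illustrative. No sample size, alpha level or primary analysis is affected.

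**What to change.** Under Analysis of the routine data, amend the cost-effectiveness paragraph as follows.

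- Report dC and dE for each informedness measure, with cluster-adjusted confidence intervals, alongside the cost-effectiveness result.
- Show their joint uncertainty on the cost-effectiveness plane, with the share in each quadrant obtained by resampling practices.
- Use incremental net benefit, λ·dE - dC, with its interval over a stated range of λ, as the summary for each measure.
- Keep the ratio with its Fieller interval only when dC and dE have the same sign, labelled by quadrant, and dE is clearly different from zero (for example, its 95% interval excludes zero).

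The cost is revised wording and a little more analysis on the same data. The real downside is that no accepted value per unit of informedness exists, so the result is a curve over λ rather than one number.
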